### Sample size

Depression has an estimated annual prevalence of 8.3 % in adolescents [12], and between 8 % and 20 % of young people in community samples develop depression over an 18-month period [51–53]. On the basis of the age of the current sample, together with the timing of the intervention (before a major, universal stressor), we expect that onset rates will be high (up to 15 %). Calculations of required sample size for the primary outcome measure were based on detecting a post-intervention effect size of 0.20 in combined analyses of data collected from 2015 and planned 2016 cohorts. This estimate is based on previous depression prevention research using an online intervention [54]. Although the expected effect is small, it reflects the universal nature of this intervention. Power was set at 0.80, α = 0.05 (two-tailed) and a correlation of 0.5 assumed between baseline and endpoint scores. To allow for possible clustering effects (i.e., participants from the same school having characteristics and outcomes more alike than between schools), a design effect [55] was calculated assuming an intraclass correlation coefficient (ICC) of 0.02 and an average class size of 25. The estimate of the ICC was derived from a previous Australian school-based study that found a non-significant ICC of 0.02 [54]. The estimated sample size was 1166. The target size sample size was set at 1600, or 800 students per condition, to accommodate an attrition rate of approximately 20 % (see [56]). This translates to approximately 50 students (or 2 classes) per school in 30 schools. An interim analysis of students in the 2015 cohort will involve approximately 300 students per arm. Under the assumptions outlined above, there will be 80 % power to detect an effect size of 0.40 standard deviations between groups.

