### Randomisation

Each participating school (cluster) will be randomised to complete the SPARX-R or lifeSTYLE program. School-level randomisation will be used to avoid contamination between conditions, for the ecological validity of providing the intervention at the cluster level and for practical convenience. A statistician not involved in the implementation of the trial will randomly allocate schools using the allocation sequence outlined below. The identity of schools will be concealed from the statistician during this process.

Randomisation in cluster randomised trials is problematic because the number of clusters involved is usually relatively small. In large, individually randomised trials, balance in the makeup of each arm is achieved as a function of the numbers involved. Balance between arms can be achieved by stratification or minimisation [57]. Stratification can accommodate only a limited number of balancing variables, and minimisation is based on incremental assignment of participants to groups. In TriPoD, the number of potentially relevant variables to be balanced between arms is quite large (e.g., sex, number of enrolled students, Index of Community Socio-Educational Advantage school index, language background other than English), and all available sites will be enumerated before commencement of the trial. Achieving approximately equal numbers of participants in each arm is also an aim of the allocation design, as this will determine the study’s power in the absence of substantial clustering effects. Accordingly, this attribute of each school will be used not to estimate the degree of balance, but rather to screen potential grouping after balanced combinations have been selected.

We will use the method developed and implemented by Carter and Hood [58] to ensure balance between intervention arms. This enumerates all possible divisions of the available schools into two groups and calculates a balance index [59] for each of these groupings. The 10 most balanced groupings will be retained after excluding any grouping resulting in a deviation of more than 10 % in predicted individual participant sample size between inventions. The allocation schedule will be selected at random from the groupings retained.

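### The design effect uses a class of 25 although whole schools of about 50 are randomised, so the stated 80% power is really about 72–75%.

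*Protocol article*

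**What the plan says.** The Sample size section of the protocol article sets out the calculation for the primary outcome:

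- Target effect: "detecting a post-intervention effect size of 0.20 in combined analyses of data collected from 2015 and planned 2016 cohorts".
- Error rates: "Power was set at 0.80" and "α = 0.05 (two-tailed").
- Baseline: "a correlation of 0.5 assumed between baseline and endpoint scores".
- Clustering, explained as "participants from the same school having characteristics and outcomes more alike than between schools".
- Inflation: "a design effect [55] was calculated assuming an intraclass correlation coefficient (ICC) of 0.02 and an average class size of 25".

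The result is 1166 students. The target is raised to 1600, 800 per arm, to cover attrition of roughly 20%. The section then adds: "This translates to approximately 50 students (or 2 classes) per school in 30 schools".

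The Randomisation section is explicit about the unit: "Each participating school (cluster) will be randomised to complete the SPARX-R or lifeSTYLE program". The Analysis section fits school as the random effect and defines the primary contrast as the between-arm difference in change on the depression score from pre-test to post-intervention.

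**The concern.** The design effect 1 + (m − 1) × ICC is meant for the unit that is randomised, with m the number of students analysed in each such unit. Here that unit is the school. Class is neither a unit of allocation nor a level in the model. Two classes from one school always receive the same programme and share the same school effect, so they are not two independent clusters. Using 25 in place of the school's size roughly halves the part of the design effect that comes from clustering.

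The target effect is small and the number of schools modest, so the shortfall matters. A null result would be read as coming from a trial with a 20% type II error when the real figure is 25–28%. Planning for the 2016 recruitment rests on the same paragraph.

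**Working it through.** **Inputs.** Effect 0.20 SD, two-sided 0.05, power 0.80, baseline–endpoint correlation 0.5, ICC 0.02, class size 25, target 1600, attrition 20%, 30 schools (all Sample size). Unit of randomisation: school (Randomisation). Contrast: change; random effect: school (Analysis).

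**1. Reproduce the plan's figure.**
- The variance of a change score with correlation 0.5 is 2 × (1 − 0.5) = 1 SD².
- A two-sample t calculation for 0.20 SD needs 394 per arm, 788 in all.
- Design effect with 25 per cluster: 1 + 24 × 0.02 = 1.48.
- 788 × 1.48 = 1166.2, matching 1166.
- A baseline-adjusted analysis would carry a variance factor of 1 − 0.5² = 0.75. It gives 786 × 0.75 × 1.48 = 872, using the normal-approximation size of 393 per arm. The plan therefore did not use that gain.

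**2. Correct the cluster size.**
- Analysed students: 1600 × 0.80 = 1280; per school, 1280 / 30 = 42.7.
- Design effect: 1 + 41.7 × 0.02 = 1.83. (At 50 per school it is 1 + 49 × 0.02 = 1.98.)
- Standard error in SD units: √(4 × 1.833 / 1280) = 0.0757.
- 0.20 / 0.0757 = 2.64.
- Normal approximation: power = Φ(2.64 − 1.96) = 0.752.
- Non-central t with 30 − 2 = 28 df: power = 0.723.

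**3. The same calculation for other numbers analysed, 30 schools.**

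| Analysed | Per school | Design effect | Power, normal | Power, t (28 df) |
|---|---|---|---|---|
| 1166 | 38.9 | 1.76 | 0.731 | 0.701 |
| 1200 (30 × 50 less 20%) | 40.0 | 1.78 | 0.738 | 0.708 |
| 1280 | 42.7 | 1.83 | 0.752 | 0.723 |
| 1600 (no loss) | 53.3 | 2.05 | 0.798 | 0.770 |

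For comparison, 25 per cluster would give 0.837 (normal) at 1280 analysed.

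**4. Detectable effect at 80% power, 1280 analysed.** Normal: (1.96 + 0.84) × 0.0757 = 0.21. With t on 28 df: 0.22.

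**5. Size needed for 80% power.**
- At 50 analysed per school: 788 × 1.98 = 1560 analysed, or 1560 / 0.80 = 1950 enrolled. This needs 1560 / 50 = 31.2 schools.
- With 30 schools held fixed, solve 30m / (1 + (m − 1) × 0.02) = 788. Then m = 788 × 0.98 / (30 − 788 × 0.02) = 54.2, so about 1627 analysed, or about 2034 enrolled.

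**6. Baseline-adjusted contrast.** With the variance factor of 0.75 and 1280 analysed at 42.7 per school, power is 0.862 (normal) or 0.838 (t).

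**7. The paragraph's totals.** 30 × 50 = 1500, not 1600 (1600 / 30 = 53.3). 1166 / 0.80 = 1458. A target of 1600 against 1166 allows a loss of 1 − 1166/1600 = 27%.

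**The case against.** Nothing in the article rescues the class size of 25, but five points can be made on the other side.

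- *The 72–75% is conditional.* It depends on an ICC borrowed from one earlier study and described as non-significant. At 1280 analysed and 42.7 per school, an ICC of 0.015 gives 80% (normal) and 0.01 gives 85%; by the same formula, 0.03 gives 66%. This stands as a caveat. It does not defend the calculation, which adopts 0.02 and speaks of schools. Even if 0.02 were a class-level value, which the article does not say, two classes in one randomised school would not be independent.
- *The 28 degrees of freedom are the reviewer's choice.* This is fair: the article names no small-sample method. Without it, power is still about 75%, not 80%.
- *The margin up to 1600 absorbs the error.* It does not. The figures above already credit that margin by analysing 1280 rather than 1166.
- *The rounding is harmless.* The article says approximately for both the 50 per school and the 20%, and 1600 errs on the safe side of 1458. The mismatches are minor by themselves and worth tidying only because the paragraph needs rewriting.
- *The loss is modest and validity is untouched.* This is true: school is in the model, so neither the estimate nor the type I error suffers. What is wrong is the power claimed for the primary contrast.

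**Conclusion.** The concern holds. The design effect was computed for a class, while the design, the allocation and the model all use the school. On the plan's own effect size, ICC, attrition and number of schools, power for the primary contrast is about 75% by the normal approximation and about 72% with 28 degrees of freedom. Even with no attrition it only just reaches 80% by the normal approximation (0.798) and falls short on t (0.770).

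The result assumes an ICC of 0.02 that applies to the change contrast, equal school sizes, and the change-score variance implied by 1166. Unequal school sizes would lower power further. The 2015 cohort suggests that schools may be larger than planned: about 300 students per arm in the ten schools listed under Trial status is 600 / 10 = 60 per school, a design effect of 1 + 59 × 0.02 = 2.18.

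**What to change.** Rewrite the sample size paragraph:

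1. Compute the design effect from students analysed per school (about 43 after attrition), with a t reference on about 28 degrees of freedom.
2. Restate the result as about 72–75% power for an effect of 0.20 with a change contrast, or 80% power for an effect of about 0.22 (0.21 by the normal approximation).
3. Make the totals agree: students per school, number of schools, the target of 1600, and the attrition it really allows.
4. If 80% power at 0.20 is to be kept without adding schools, define the primary contrast as adjusted for baseline and say so in both the Sample size and Analysis sections. On the same inputs, power is then about 84–86%. The gain depends on the assumed correlation of 0.5.

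The first three changes cost only rewording, and the stated power becomes less favourable. The fourth changes how the primary contrast is specified but needs no new data. Because post-intervention data from the 2015 cohort already exist, it should be recorded as a dated amendment made without reference to results by arm.

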### Analysis

Primary analyses will be undertaken on an intention to treat basis, including all participants as randomised, regardless of treatment actually received. Effectiveness of SPARX-R will be established using a planned contrast of change from pre-test to the post-intervention in the active compared with placebo condition on the MDI within a mixed-effects model repeated-measures analysis [104]. School will be included in analyses as a random effect to evaluate and accommodate clustering effects. Variables used in determining allocation balance will be evaluated and retained in analyses where they are significant or quasi-significant. An unconstrained variance–covariance matrix will model within-individual dependencies. Transformation of scores, including categorisation, may be undertaken to meet distributional assumptions and accommodate outliers. Contrasts comparing change on the MDI from pre-test to other occasions of measurement will be undertaken as secondary analyses.

Models for binary outcomes analogous to the primary analysis approach will be used to compare the prevalence rates (MDD status) and other dichotomous outcomes between the two treatment arms at the endpoint and other occasions of measurement. Relative and absolute risk reduction, NNT (see [105]) and other relevant indices will be calculated for these outcomes and undertaken separately for participants who did not meet criteria for caseness at pre-test to assess the effect of the intervention on incidence. In analyses of scaled secondary variables, we will use methods comparable to those of the primary analysis. Subsidiary complier and related analyses will estimate the efficacy of SPARX-R in participants who completed modules from the SPARX-R program to produce a clinical impact (estimated to be four or more modules) [36]. In exploratory analyses, we will examine the effects of moderators and mediators of treatment (see [106]).

Interim analysis of outcomes of the 2015 cohort will be undertaken following the methods described above. Although the sample available will be of limited size, the outcome of this analysis will be used to guide the second stage of the trial, planned for 2016. Should there be clear evidence of lack of effect, based point estimates of effectiveness and associated confidence intervals, consideration may be given to abandoning second-stage recruitment or seeking possible modifications of the intervention.

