## Trial status

Twenty-three selective or partially selective high schools were approached to participate in the trial between August and October, 2014. Fourteen of the schools agreed to participate; however, four schools subsequently withdrew from the study. The final sample for the 2015 cohort consisted of two partially selective and eight selective government secondary schools. The 2015 cohort of schools completed their baseline assessments in February, 2015, followed by their respective online programs. All post-intervention assessments were completed by April, 2015 and six-month follow-up data was collected in August, 2015. Educational outcomes (HSC results) and 18 month follow-up data will be collected in 2016 for this cohort.

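### The interim detectable effect of 0.40 SD does not follow from the assumptions it is attributed to; those give 0.28 to 0.31, and 0.40 needs a basis the plan does not state

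*Protocol article*

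**What the plan says.** The Sample size section of the protocol article sizes the trial for the pooled data, "based on detecting a post-intervention effect size of 0.20 in combined analyses of data collected from 2015 and planned 2016 cohorts". Its inputs are given as "Power was set at 0.80, α = 0.05 (two-tailed) and a correlation of 0.5 assumed between baseline and endpoint scores", and the design effect was computed "assuming an intraclass correlation coefficient (ICC) of 0.02 and an average class size of 25". The result is "The estimated sample size was 1166", raised to 1600 "to accommodate an attrition rate of approximately 20" %. The section then puts the 2015 interim analysis at about 300 students per arm and states that, on these same assumptions, there will be 80% "power to detect an effect size of 0.40 standard deviations between groups".

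The Analysis section uses that interim result to guide the second stage, while acknowledging that the 2015 sample is small. The condition it sets is "Should there be clear evidence of lack of effect, based point estimates of effectiveness and associated confidence intervals"; if that is met, the investigators may consider giving up second-stage recruitment or changing the intervention.

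The Trial status section reports that "The final sample for the 2015 cohort consisted of two partially selective and eight selective government secondary schools", that is, ten schools. Under Randomisation, whole schools are allocated, and under Analysis, school enters the model as a random effect.

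**The concern.** The interim figure is presented as a consequence of the assumptions behind 1166, yet the two cannot come from the same calculation. For a fixed method, the detectable effect scales with one over the square root of the sample size. Going from 1166 to 600 students should therefore move it from 0.20 to about 0.20 x sqrt(1166/600) = 0.28, not to twice its value.

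The figure matters because it is the only statement of what the 2015 look can show, and that look may influence whether stage two goes ahead. Whoever weighs the 2015 estimate and interval needs to know how precise they are and how likely the look is to detect the planned 0.20. As printed, the section gives a detectable effect with the wrong basis and no power for 0.20.

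**Working it through.** **Inputs.** From Sample size: alpha 0.05 two-sided, power 0.80, r = 0.5, planned effect 0.20, ICC 0.02, class size 25, attrition about 20%, about 300 per arm at the interim. From Trial status: ten schools in 2015. Assumed: five schools per arm, equal school sizes, and a variance factor of 2(1 - r) = 1.0, as for change scores. The article does not say whether 300 per arm is before or after attrition, so both 300 and 240 (= 300 x 0.8) are shown.

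**Step 1: reproduce 1166.** Design effect = 1 + (25 - 1) x 0.02 = 1.48. A two-sample t-test for 0.20 needs 394 per arm. Then 2 x 394 x 1.48 = 1166.2, which matches the stated total and identifies the method.

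**Step 2: same method at the interim.** SE = sqrt(2 x 1.48 / n); detectable effect = (1.960 + 0.842) x SE; power at d = Phi(d/SE - 1.960).
- n = 300: SE = 0.0993, detectable effect 2.802 x 0.0993 = 0.278. Power at 0.40: Phi(4.03 - 1.96) = 98%. Power at 0.20: Phi(2.01 - 1.96) = 52%.
- n = 240: SE = 0.1111, detectable effect 0.311. Power at 0.40: 95%. Power at 0.20: 44%.

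**Step 3: ten schools as the clusters.**
- 60 students per school: design effect 1 + 59 x 0.02 = 2.18, SE = sqrt(2 x 2.18/300) = 0.1206.
- 48 per school after attrition: design effect 1 + 47 x 0.02 = 1.94, SE = sqrt(2 x 1.94/240) = 0.1271.

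The 8-df rows below use the noncentral t distribution with 10 - 2 = 8 degrees of freedom.

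| Basis | Detectable effect (300 / 240 per arm) | Power at 0.20 (300 / 240 per arm) |
|---|---|---|
| Stated: classes of 25, normal | 0.28 / 0.31 | 52% / 44% |
| Ten schools, normal | 0.34 / 0.36 | 38% / 35% |
| Ten schools, t with 8 df | 0.39 / 0.41 | 31% / 28% |

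**Step 4: other routes to 0.40.** About 300 students in total (150 per arm, design effect 1.48) gives 0.394. So does 300 per arm with a variance factor of 2, which ignores r = 0.5. Neither is what the text says, and the article does not show which route was used.

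**Step 5: what the 2015 interval could exclude.**
- Stated assumptions: the 95% half-width is 1.96 x 0.0993 = 0.19 to 1.96 x 0.1111 = 0.22. An estimate of zero then just excludes, or just fails to exclude, 0.20.
- Ten schools with 8 df (t quantile 2.306): the half-width is 2.306 x 0.1206 = 0.28 to 2.306 x 0.1271 = 0.29. Here 0.20 is excluded only if the estimate favours control by about 0.08 (0.28 - 0.20) to 0.09 (0.29 - 0.20).

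How a flat 2015 result should be read therefore depends on which basis is meant.

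**Sensitivity.** With a baseline-adjusted variance factor of 1 - r² = 0.75, power at 0.20 is 64% / 55% on the stated clustering and 39% / 36% with ten schools and 8 df. That factor does not reproduce 1166: 788 x 0.75 x 1.48 = 875.

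**The case against.** The strongest defence is that the printed number is close to the truth for the cohort actually recruited. With ten schools as clusters and 8 degrees of freedom the detectable effect is 0.39 to 0.41, so a correction on that basis would change the explanation more than the number. On the stated assumptions the slip is conservative, since 300 per arm has more power than claimed. It touches neither 1166, nor 1600, nor the primary analysis. A careful reader can also see that the look is sized for twice the planned effect. All of this stands and limits the weight of the point, but it does not repair a sentence that names the wrong assumptions.

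Four stronger readings are tempting, and the article does not support them.
- A reader might infer that the look has only about 30% power for 0.20. That needs school clusters, the assumed even split and 8 degrees of freedom, a basis on which 0.40 is about right. On the stated assumptions power is 52%, or 44% after attrition. The two criticisms cannot be drawn from one basis.
- A reader might infer that a non-significant 2015 result would end the trial. The Analysis section asks for clear evidence, judged on estimates and intervals, and then only permits consideration.
- A reader might infer an inflated type I error from testing twice. No early efficacy claim or efficacy stop is planned, and the trial is powered on the combined data.
- A reader might fault the lack of a numerical futility threshold. That is commonly left to an analysis plan, which is not at hand, and any particular cut-off would be a matter of preference.

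**Conclusion.** The point holds as an error of stated basis, at should-fix level. Under the assumptions the section names, the interim detectable effect is 0.28 (0.31 after 20% attrition) instead of 0.40, and power at 0.40 is 98% (95%) instead of 80%. This rests on the variance factor of 1.0 and design effect of 1.48 that reproduce 1166.

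Of the unstated routes to about 0.40, the school-level one fits the design best, because schools are randomised and modelled as a random effect. It rests on the assumed 5:5 split and on 48 to 60 students per school.

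On every basis in the table, power for 0.20 is well below 80%, so a non-significant 2015 result would be unremarkable even if the planned effect were real. This supports a clarifying sentence about interpretation; it does not show that the plan's condition for reconsidering stage two is wrong.

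**What to change.** 1. In the Sample size section, reconcile 300 per arm, the design effect and 0.40. Either state 0.28 to 0.31 on the listed assumptions, or state about 0.39 to 0.41 and name its basis (ten schools as clusters, number of students per school, 8 degrees of freedom). The second is preferable because it matches the randomisation and the school random effect. Say whether 300 per arm is before or after attrition.
2. Beside it, report interim power for the planned 0.20: 44-52% on the listed assumptions, 35-38% with school clusters and a normal reference, 28-31% with 8 degrees of freedom.
3. In the Analysis section, add that a non-significant 2015 result is not in itself evidence of lack of effect, and that the confidence interval is to be read against the planned 0.20.

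The cost is a few sentences in the protocol or analysis plan. The sample size, the primary analysis and the freedom to reconsider stage two are unchanged.

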### Randomisation

Each participating school (cluster) will be randomised to complete the SPARX-R or lifeSTYLE program. School-level randomisation will be used to avoid contamination between conditions, for the ecological validity of providing the intervention at the cluster level and for practical convenience. A statistician not involved in the implementation of the trial will randomly allocate schools using the allocation sequence outlined below. The identity of schools will be concealed from the statistician during this process.

Randomisation in cluster randomised trials is problematic because the number of clusters involved is usually relatively small. In large, individually randomised trials, balance in the makeup of each arm is achieved as a function of the numbers involved. Balance between arms can be achieved by stratification or minimisation [57]. Stratification can accommodate only a limited number of balancing variables, and minimisation is based on incremental assignment of participants to groups. In TriPoD, the number of potentially relevant variables to be balanced between arms is quite large (e.g., sex, number of enrolled students, Index of Community Socio-Educational Advantage school index, language background other than English), and all available sites will be enumerated before commencement of the trial. Achieving approximately equal numbers of participants in each arm is also an aim of the allocation design, as this will determine the study’s power in the absence of substantial clustering effects. Accordingly, this attribute of each school will be used not to estimate the degree of balance, but rather to screen potential grouping after balanced combinations have been selected.

We will use the method developed and implemented by Carter and Hood [58] to ensure balance between intervention arms. This enumerates all possible divisions of the available schools into two groups and calculates a balance index [59] for each of these groupings. The 10 most balanced groupings will be retained after excluding any grouping resulting in a deviation of more than 10 % in predicted individual participant sample size between inventions. The allocation schedule will be selected at random from the groupings retained.

